#### Compliance

Compliance with the exercise training programme (i.e. attendance at each training session) and nutritional supplement (i.e. consumption) will be assessed via attendance record and self-reported diaries, respectively. Diaries will be monitored weekly and calendars will be monitored monthly by the participant’s accredited exercise physiologist and researchers. In addition to the calendars, compliance with the sachets and vitamin D tablets will be checked by counting all returned at the 26- and 52-week testing sessions.

#### Adverse events

Any adverse events potentially associated, or confirmed to be associated, with the exercise programme or protein, calcium and vitamin D supplementation will be recorded by the exercise trainers at each exercise training session for the intervention-group participants and monthly telephone calls by the research staff to the control-group participants. For this trial, an adverse event will consist of any health-related unfavourable or unintended medical occurrence (e.g. sign, symptom, syndrome, illness) that develops or worsens during the trial. All adverse events will be assessed for seriousness, causality and expected outcome by the researchers and followed during the trial. Although there will be no formal data monitoring committee, all data will be reviewed at regular intervals throughout the study and researchers involved in recruitment, testing and implementing the trial will update the research team monthly about the study progress.

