### Measurements

All measures will be collected at baseline, 26 and 52 weeks. Additionally, 24-h food recalls will also be administered at 13 and 39 weeks to monitor any habitual fluctuations in dietary factors. With the exception of blood samples, 24-h food recalls and questionnaires, all data will be collected at Deakin University. Blood samples will be collected at an external commercial pathology clinic. The 24-h food recalls will be administered via telephone. Questionnaires will be completed by participants at home prior to each testing sessions (i.e. baseline, 26 and 52 weeks) and checked by the research staff during these face-to-face testing sessions. A summary of the proposed outcome measures is shown in Table 2. All participants will undergo all measures expect those specific to treatment allocation (i.e. compliance to the intervention). All data collected will be in a continuous format, aside from the outcomes from some of the questionnaires, which will be categorical in nature.

**Table 2 Tab2:** Summary of data collection

Variables	Data collection method	Data collection points		
		Baseline	26 weeks	52 weeks
Primary outcome measures				
Areal bone mineral density	DXA proximal femur and lumbar spine	x	x	x
Secondary outcome measures				
Bone structure and strength	pQCT scan at 4% and 66% radial and tibial site	x	x	x
Body composition	DXA total body and regional lean mass, fat mass and % body fat	x	x	x
	pQCT 66% radial and tibial muscle cross-sectional area and muscle density	x	x	x
Muscle strength	Chest press, leg press and seated row	x	x	x
	Grip strength	x	x	x
Functional capacity	30-s sit-to-stand	x	x	x
	Timed-up-and-go with cognitive task	x	x	x
	Four-square step test	x	x	x
	Berg balance scale	x	x	x
	Four-metre usual walk	x	x	x
	400-metre walk	x	x	x
Biochemistry and lipids	Overnight, fasted serum and plasma collection	x	x	x
Inflammatory markers	Overnight, fasted serum and plasma collection	x	x	x
Blood pressure	Automated measurement	x	x	x
Cognitive function	CogState Brief Battery computerised tests	x	x	x
	Rey Auditory Verbal Learning Test	x	x	x
	Trail Making Test (Part A and B)	x	x	x
	Digit Span Test	x	x	x
	National Adult Reading Test	x		
Health-related quality of life, fatigue and mood	Functional Assessment of Cancer Therapy-Fatigue questionnaire	x	x	x
	Functional Assessment of Cancer Therapy-Prostate questionnaire	x	x	x
	Assessment of Quality of Life 8D questionnaire	x	x	x
	Geriatric Depression Scale questionnaire	x	x	x

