	Depression Anxiety and Stress Scale questionnaire	x	x	x
Additional measures				
Anthropometry	Height, weight, Body Mass Index, waist and hip circumference	x	x	x
Habitual physical activity	Community Healthy Activities Model Programme for Seniors physical activity questionnaire	x	x	x
Diet	24-h food recalls	Collected every 13 weeks		
Additional questionnaire	Demographic questionnaire	x		
	Clinical and lifestyle questionnaire	x	x	x
	Sun exposure habits and practices questionnaire	x	x	x
	Alcohol consumption questionnaire	x	x	x
	Medical questionnaire	x	x	x
	Medication questionnaire	x	x	x
	Falls questionnaire	x	x	x
Exercise programme adherence	Calculated from monthly calendars collected every 4 weeks	Collected every 4 weeks		
Supplement compliance	Calculated from supplement returned at 26 and 52 weeks		x	x
Adverse events	Calculated from monthly calendars collected every 4 weeks	Collected every 4 weeks		

*DXA* dual-energy X-ray absorptiometry, *pQCT* peripheral quantitative computed tomography

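### Adverse events are collected differently in the two arms and under a scope that contradicts the protocol's own definition, so a between-arm count from these sources would be biased

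*Protocol article*

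**What the plan says.** The Protocol article describes adverse-event collection in two places.

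- **Section Adverse events, collection.** Events are "recorded by the exercise trainers at each exercise training session for the intervention-group participants and monthly telephone calls by the research staff"; the calls go to the control arm.
- **Same section, scope.** The sentence on recording covers "Any adverse events potentially associated, or confirmed to be associated, with the exercise programme or protein, calcium and vitamin D supplementation". The next sentence says that "an adverse event will consist of any health-related unfavourable or unintended medical occurrence", with no link to treatment required. The one after that adds: "All adverse events will be assessed for seriousness, causality and expected outcome by the researchers and followed during the trial".
- **Section Measurements, Table 2.** The source for adverse events is "Calculated from monthly calendars collected every 4 weeks", with no difference by arm. The text above the table says: "All participants will undergo all measures expect those specific to treatment allocation (i.e. compliance to the intervention"). Table 2 also schedules falls and medical questionnaires at baseline, 26 and 52 weeks, and the section Additional questionnaires includes falls and fracture history.

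Three other sections bear on the point. Usual-care control group gives controls 1000 IU of vitamin D a day but neither the exercise nor the sachet. Multi-component exercise programme sets two supervised gym sessions a week for 26 weeks, then one, and leaves home sessions unsupervised. Randomisation and blinding states that participants and testing researchers are not blinded, apart from the independent assessment of the DXA and pQCT scans.

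**The concern.** A count of adverse events depends on how often men are asked, by whom, and which events qualify. Here all three differ, or may differ, by arm.

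A trainer who sees a man once or twice a week will hear of soreness, strains and passing illness that may be forgotten by the time of a monthly call. If only events thought to be related to treatment are recorded, a sore knee can qualify in a man who trains and be left out in a man who does not. Both mechanisms push the same way, towards more recorded events in the intervention arm.

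The programme progresses to high-impact loading in men whom the Background describes as being at raised risk of fracture, so readers will want to know whether it is safe. A safe programme could look harmful. Equally, without background events from controls recorded on the same terms, the trial could not show that events in the intervention arm are no more than expected.

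**Working it through.** The plan states no figure for this point, so there is none to reproduce. The check has three parts.

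**1. Scheduled contacts over 52 weeks**

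- Supervised sessions, intervention arm: 2 × 26 + 1 × 26 = 78.
- Calls, control arm: 12 if monthly, 13 if every 4 weeks.
- Ratio at full attendance: 78/13 = 6.0 to 78/12 = 6.5.
- Attendance will not be complete. Borrowing the 66% exercise threshold of the per-protocol analysis as an illustration: 0.66 × 78 ≈ 51 contacts, and 51/13 ≈ 3.9 to 51/12 ≈ 4.3.

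Home sessions and the unsupervised gym sessions are left out because no trainer is scheduled to be present.

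**2. The statements on scope and source, side by side**

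| Place | Which events | Source |
|---|---|---|
| Adverse events, recording sentence | Potentially or confirmed to be associated with exercise or supplementation | Trainers at sessions; staff calls to controls |
| Adverse events, definition | Any unfavourable or unintended occurrence | Not stated |
| Adverse events, assessment | All events, each assessed for causality | Not stated |
| Table 2 | Not stated | 4-weekly calendars, no arm difference given |

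Rows 1 and 2 conflict. Row 3 fits row 2 but not row 1: if attribution decides what is recorded, the later causality assessment sees only events that have already been filtered. The filter is also unequal. An intervention-arm event can qualify through exercise, sachet or vitamin D; a control-arm event can qualify only through vitamin D.

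Row 4 is a source that the Adverse events section does not mention. The sentence on who undergoes the measures suggests that controls keep calendars. However, Table 2 uses the same calendars for exercise adherence, and the Compliance section has them monitored by the exercise physiologist and researchers. No sentence says outright that controls complete them.

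**3. What unequal capture could do to a comparison**

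This is an illustration. The documents give neither event proportions nor capture rates, so both are assumed. Take 51 men per arm, the same true risk in both, and control-arm capture equal to a fraction *c* of intervention-arm capture. If the proportion of men with a recorded event is *p* in the intervention arm, it is *cp* in controls, and the apparent risk ratio is 1/*c*. The chance of a significant excess in the intervention arm (normal approximation, two-sided 5% test) is

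Φ{[(p − cp) − 1.96·√(2p̄(1 − p̄)/51)] / √[(p(1 − p) + cp(1 − cp))/51]}, where p̄ = (p + cp)/2.

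For p = 0.40 and c = 0.8: difference 0.08, p̄ = 0.36, standard errors 0.0950 (pooled) and 0.0947. This gives Φ{(0.08 − 0.186)/0.0947} = Φ(−1.12) = 0.13.

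| Relative capture *c* | Apparent risk ratio | p = 20% | p = 40% | p = 60% |
|---|---|---|---|---|
| 0.8 | 1.25 | 8% | 13% | 23% |
| 0.6 | 1.67 | 19% | 41% | 68% |

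With equal capture the ratio is 1.0 and the chance is 2.5% in that direction, half of the nominal 5%.

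**The case against.** The strongest case on the other side has five parts.

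- **The arms share some instruments.** Falls and medical questionnaires are given to all participants at 26 and 52 weeks, with falls and fracture history included. A reader might infer from the Adverse events section that harms cannot be compared at all. The documents do not support that: falls, fractures and medical conditions have a common instrument and schedule. This stands. It is partial protection only, because the questionnaires are six-monthly and are not named as an adverse-event source.
- **The filter is not settled, and controls do receive something.** A reader might infer that controls can contribute few or no events because they get none of the treatment. They get 1000 IU of vitamin D a day, monthly calls are planned for this very purpose, and potential association is a broad test. The next sentences also point to unrestricted recording. So the finding is a contradiction on scope, not a fixed restriction.
- **Calendars may already be common to both arms.** Calendars and session or telephone recording can coexist, and a condensed article may simply describe them incompletely. That is possible, but the article does not establish it.
- **No between-arm test of adverse events is stated.** They are listed among additional measures, not outcomes. This stands: the bias arises only if counts are set side by side by arm, which is likely in any report but is not promised here.
- **Contacts are not captured events.** Fractures and cardiac events are likely to be reported at a monthly call too. This stands, and it confines the expected distortion mainly to minor events.

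**Conclusion.** The concern holds in a limited form. Following the Adverse events section as written gives arm-dependent ascertainment, with about 4 to 6.5 times as many scheduled contacts in the intervention arm depending on attendance, and no blinding to offset it. Its recording sentence contradicts its own definition and its causality assessment. Its sources need to be reconciled with Table 2.

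Any comparison of event counts based on the session and telephone sources would be biased, most likely towards an apparent excess of minor events in the intervention arm. The direction follows from the design. The size is not known: the apparent risk ratios of 1.25 and 1.67 rest on assumed relative capture of 80% and 60%, and the chances of a false signal also rest on assumed event proportions and on all 51 men per arm contributing. It would go too far to say that no harms comparison is possible, or that the 6.5-fold ratio of contacts implies a 6.5-fold ratio of recorded events.

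**What to change.** - Reconcile the Adverse events section with Table 2, so that both name the same sources.
- Replace the recording sentence with one that records all adverse events regardless of suspected cause, and keep attribution for the causality assessment that follows.
- State that the 4-weekly calendar, with the same scripted monthly question, is used in both arms.
- Base any between-arm comparison of harms on that common source and on the common questionnaires only.
- List events noted only at training sessions separately, as intervention-arm safety data. They remain fully reported but do not enter the comparison.

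The cost is a wording change, a little staff time for the monthly question to intervention men, and calendars for controls if they do not already have them. The comparative table will hold fewer events than the total recorded. The Trial status section says that recruitment is under way, so the change can still improve data yet to be collected; events gathered before it should be identified as such.

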#### Data management and archiving

All data will be stored on password-protected computers and in locked filing cabinets at Deakin University (Burwood). All study-related documents will be archived at Deakin University at the end of the study for 7 years which is in line with current ethical requirements.

#### Dissemination plan

Findings from the primary outcomes of this trial will be reported in journal articles, which will include results regardless of the direction or magnitude of the effect. The results will also be presented at leading national and international conferences, clinical forums and to other relevant health professionals and stakeholders, as well as to the participants. All investigators will have the opportunity to be listed as an author of future publications in accordance with journal-specific guidelines.

### Sample size calculation

The sample size calculations are based on our previous research in healthy and ADT-treated men. The mean (standard deviation (SD)) annual loss in femoral neck, hip and spine BMD in ADT-treated men was 3.0% (4.5), 2.6% (2.8) and 3.9% (3.0), respectively [14]. Our previous exercise trials in healthy older men have shown that 12 months of training can increase spine aBMD by 1.5–2.0% (SD 2.9) and hip aBMD by 1.2–1.8% (SD 2.8) [39, 55]. We estimate a conservative net difference in aBMD in favour of the intervention of ~ 3.5–4.0% at the hip and spine. Based on these estimates, 29 men in each group will provide 90% power (*P* < 0.05, two-tailed) to detect a difference of this magnitude (assuming a SD of 4.0). A net benefit of this magnitude is clinically relevant as there is evidence that a 1–2% gain in aBMD translates into a 7–14% reduction in fracture risk [36, 93]. For pQCT bone measures, radial and tibial cortical area decreased by 11.5% (8.8) and 12.5% (7.4), respectively, over 12 months in ADT-treated men [14]. While few long-term trials have examined the effect of exercise training on pQCT bone geometry in older men, several intervention trials in older adults have shown that a targeted, weight-bearing, impact-exercise programme can have beneficial effects on cortical bone [94, 95]. Assuming that the proposed intervention can half the rate of loss in cortical area, we estimate that we will require 39 men per group (SD 8.0; 90% power, two-tailed, *P* < 0.05). Based on a previous study and a meta-analysis showing that ADT is associated with an average 7.7% gain in fat and a 2.8% loss in lean mass over 3–12 months [96, 97], and that exercise training can prevent the gain in FM and increase (1–5%) or preserve LBM relative to usual care in men on ADT [30, 32], we estimate a sample size of 24–32 in each group will be required to observe a preservation in LBM and FM in the intervention group vs. usual care (90% power, two-tailed, *P* < 0.05). Assuming a conservatively projected 30% dropout, an estimated sample size of 51 men per group (102 in total) will be required. Based on previous studies in ADT-treated men focussing on a number of our secondary outcomes [32, 37, 98], we estimate that we will have sufficient power (80–90%, *P* < 0.05, two-tailed) to detect the following intervention effects: 20–40% for muscle strength; 8–22% for functional capacity; 4 points for fatigue (FACT-F), 15% for fasting plasma glucose and 14% for serum IL-6 and 20% for CRP. We will also have sufficient sample to detect a clinically meaningful difference of 0.5 SD in the Assessment of Quality of Life 8D questionnaire (AQoL-8D) and 9 points on the FACT-P (disease-specific QoL).

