#### Volumetric BMD, bone geometry and strength

Proximal (66%) radial and tibial cortical vBMD (mg/cm^3^), cortical area (mm^2^), total bone area (mm^2^), medullary area (mm^2^) and polar Strength Strain Index (SSIpolar, mm^3^), and distal (4%) radial and tibial total and trabecular vBMD (mg/cm^3^), total bone area (mm^2^) and the Bone Strength Index (BSI, mg^2^/mm^4^) of the non-dominant upper limb and dominant lower limb will be assessed using pQCT (XCT 3000, Stratec Medizintechnik GmbH, Pforzheim, Germany). Briefly, tibial length will be determined by measuring from the distal edge of the medial malleolus to the medial joint cleft of the knee and radial length will be determined by measuring ulnar length from the ulnar styloid process to the olecranon. After obtaining a scout-view slice of the distal endplate of the radius or tibia, scans will be performed at the 4% and 66% sites. The slice thickness will be 1 mm and voxel size will be 0.5 mm at a scanning speed of 20 mm/s. All pQCT bone and body composition parameters will be assessed using BoneJ [60] ImageJ-plugin (rsbweb.nih.gov/ij) as previously reported [61]. Distal radial and tibial (4%) total bone area and density will be analysed based on thresholding at 169 mg/cm^3^, with trabecular density assessed using a threshold of 480 mg/cm^3^. BSI will be calculated as follows: BSI = total area multiplied by the square of total vBMD [62]. For the proximal radius and tibia (66%), the periosteal surface will be determined based on a threshold of 280 mg/cm^3^, and cortical bone a threshold of 710 mm/cm^3^. Medullary area will be calculated by subtracting cortical area from total area. SSIpolar will be determined using the bone threshold of 480 mg/cm^3^ [63]. The short-term CVs for repeated measures in a sample of healthy premenopausal women range from 0.9 to 2.2% for the 4% radius, 0.7 to 2.5% for the 4% tibial and 0.6 and 1.8% for the 66% tibial outcome measures [64].

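### The 90% power stated for cortical area at 39 men per group averages two sites; on the plan's own figures it is about 81% at the radius and 96% at the tibia

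*Protocol article*

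**What the plan says.** All the figures are in the Sample size calculation of the protocol article.

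- Inputs by site: "radial and tibial cortical area decreased by 11.5% (8.8) and 12.5% (7.4), respectively, over 12 months in ADT-treated men". The bracketed values are SDs.
- Effect: "Assuming that the proposed intervention can half the rate of loss in cortical area".
- Result: "we estimate that we will require 39 men per group (SD 8.0; 90% power, two-tailed, *P* < 0.05". No site is named, and the source of 8.0 is not explained.
- Other requirements in the same paragraph: for areal bone mineral density (aBMD), "29 men in each group will provide 90% power"; for lean and fat mass, 24 to 32 per group.
- Total: "Assuming a conservatively projected 30% dropout", the article concludes that "an estimated sample size of 51 men per group (102 in total) will be required".

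The section on volumetric BMD, bone geometry and strength lists cortical area at the 66% site for both the radius and the tibia, measured on an upper and a lower limb. The section on primary and secondary outcome measures places tibial and radial bone structure among the secondary outcomes. Neither section defines a combined radius-tibia measure.

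**The concern.** The plan prints two pairs of inputs and then gives one requirement with an SD that belongs to neither site. The radius has both the smaller expected effect and the larger SD, so a single averaged calculation flatters it and understates the tibia. The outcomes will be reported site by site, so a power attached to cortical area as a whole describes a quantity the trial does not measure.

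The figure also carries weight in the design. At 39 it is the largest requirement listed, and 39 × 1.3 = 50.7 matches the 51 per group. At stake is whether the stated type II error of 10% holds for each of the two outcomes it appears to cover.

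**Working it through.** **Inputs** (all from the Sample size calculation, in percentage points): two-sided alpha 0.05; power 90%; 39 per group; planning SD 8.0; radius loss 11.5, SD 8.8; tibia loss 12.5, SD 7.4; effect equal to half the loss.

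- Radius effect: 11.5 / 2 = 5.75
- Tibia effect: 12.5 / 2 = 6.25
- Average effect: (5.75 + 6.25) / 2 = 6.0
- Average SD: (8.8 + 7.4) / 2 = 8.1, close to the stated 8.0

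**Formulas.** Two independent means, equal groups.

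- Normal approximation for size: n = 2 × (SD/Δ)² × (1.960 + 1.282)², where the last factor is 10.51.
- Power: noncentral t with 2(n − 1) degrees of freedom and noncentrality Δ / (SD × √(2/n)). At n = 39, √(2/39) = 0.2265.

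**Reproducing the stated 39.** With Δ = 6.0 and SD 8.0, the normal approximation gives 2 × (8.0/6.0)² × 10.51 = 37.4, so 38. The t-test gives 38.35, so 39, with 90.5% power at 39. Working back from 39 men, SD 8.0 and 90% power, the detectable difference is 5.95 by the t-test. This again points to an averaged effect of about 6.0. With SD 8.0, the radial effect alone would need 42 and the tibial effect alone 36.

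**Site by site at 39 analysable men per group.**

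| Case | Δ | SD | Noncentrality | Power (t) | Power (normal) | n per group for 90% (t) |
|---|---|---|---|---|---|---|
| Averaged inputs | 6.0 | 8.0 | 3.31 | 90.5% | 91.2% | 39 |
| Radius | 5.75 | 8.8 | 2.89 | 81.3% | 82.3% | 51 |
| Tibia | 6.25 | 7.4 | 3.73 | about 96% | 96.2% | 31 |

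The radial shortfall against the stated figure is 90 − 81.3 = 8.7 points. The radial type II error is about 19% instead of 10%.

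**Which average causes it.** Starting from the averaged case (90.5%):

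- SD changed to 8.8, effect kept at 6.0: 84.4%
- Effect changed to 5.75, SD kept at 8.0: 88.0%
- Both changed: 81.3%

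The SD accounts for the larger part, but neither change alone gives 81%. Even with the stated SD of 8.0, power at the radius is below 90%.

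**The case against.** The strongest reply is that nothing has been miscalculated. The planning SD is stated openly beside both site SDs, and the same paragraph also uses one SD (4.0) for aBMD sites whose SDs are 4.5, 2.8 and 3.0. This stands: 39 follows from averaged inputs, and a reader who infers an arithmetic error would be wrong.

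A reader might also infer that the trial is too small or that its main conclusion is at risk. The document does not support that. Cortical area is one of many secondary outcomes, and the 29 per group for aBMD rests on other inputs. For several other secondary outcomes the article treats 80–90% as sufficient, and 81% falls within that range. If all 51 randomised men per group were measured, radial power would be 90.5%. That is a best case, because imputing missing values does not restore lost information.

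Another tempting inference is that a null radial result would be over-read. That is speculation: the Statistical analysis section provides for 95% confidence intervals, and these show what a null result can exclude.

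The site SDs are themselves estimates, and the article does not give the size of the cited study. Assuming 20 to 50 men, the relative standard error of an SD, 1/√(2(n − 1)), is about 16% to 10%. The gap between 8.8 and 8.0 is 10% of 8.0. So 81% is a planning value, not a precise one. The uncertainty runs both ways, however, and does not make 8.0 the radial input.

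Finally, the planned analysis is a linear mixed model with possible covariates, not a t-test. Any gain in precision cannot be quantified from the article, and the stated 39 is itself reproduced by a t-test.

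None of this makes the 90% true at the radius on the inputs printed beside it.

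**Conclusion.** The point holds as a problem of planning inputs. One power figure is given for two separately defined outcomes, and the plan's own site figures do not support it at one of them. With 39 analysable men per group, power to detect a halved loss is about 81% at the radius and about 96% at the tibia. For 90%, the radius needs 51 analysable men per group and the tibia 31.

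This rests on a two-sample t-test at two-sided 0.05, on the printed losses and SDs, and on the inference that the unprinted planning effect was about 6.0. The site-specific powers do not depend on that inference.

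The weight is moderate. The calculation sets the enrolment figure, but the outcome is secondary and the primary calculation is unaffected. The point does not depend on how dropout was allowed for, since it holds with 39 complete men per group; the dropout inflation is a separate matter.

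**What to change.** In the Sample size calculation, replace the single cortical-area statement with site-specific ones. For example: with 39 analysable men per group, power to detect a halving of cortical area loss (two-sided 0.05) is about 96% at the tibia (difference 6.25%, SD 7.4) and about 81% at the radius (difference 5.75%, SD 8.8). Drop the 90% claim for radial cortical area and leave enrolment unchanged.

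The cost is one sentence, with no extra men or procedures. The downside is a less favourable stated power for one secondary outcome.

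### With 30% dropout, 51 men per group leaves about 36, not the 39 stated as required for cortical area; the primary outcome is unaffected

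*Protocol article*

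**What the plan says.** The Sample size calculation section gives three requirements per group before dropout, each at 90% power and a two-tailed 5% level.

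- **Areal BMD (primary):** "29 men in each group will provide 90% power", for a net difference of about 3.5–4.0% with an SD of 4.0.
- **pQCT cortical area (secondary):** "we estimate that we will require 39 men per group (SD 8.0; 90% power, two-tailed". The control-group loss comes from earlier data, in which "radial and tibial cortical area decreased by 11.5% (8.8) and 12.5% (7.4), respectively, over 12 months in ADT-treated men". The effect is set by "Assuming that the proposed intervention can half the rate of loss in cortical area".
- **Lean and fat mass (secondary):** "we estimate a sample size of 24–32 in each group will be required to observe a preservation in LBM and FM".

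The section then moves straight to the enrolment target: "Assuming a conservatively projected 30% dropout, an estimated sample size of 51 men per group (102 in total) will be required". It does not show how dropout was applied or say which requirement was carried forward.

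The Statistical analysis section adds that endpoint measures will be sought from men who withdraw, that linear mixed models will be used, and that missing data from men lost to follow-up will be multiply imputed.

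**The concern.** An allowance for dropout should leave the required number of men after the assumed loss. If a fraction d is lost, the number to randomise is the required number divided by (1 − d). Multiplying by (1 + d) is a common slip that always gives too few. Here the final figure agrees with the multiplied version of the largest requirement, and no stated requirement gives it by division.

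At stake is the 90% power stated for cortical area. At the dropout rate the article itself assumes, that power is not quite reached, and a reader interpreting a null cortical result would rely on a figure slightly too favourable.

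**Working it through.** **Inputs** (all from the Sample size calculation section): requirements of 29, 39 and 24–32 per group; dropout 30%; final size 51 per group, 102 in total; cortical area SD 8.0; areal BMD difference 3.5–4.0%, SD 4.0.

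**Step 1: reproduce the pre-dropout figures.** Method: two-sample t-test, two-sided 0.05, 90% power.

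- Cortical area: half of 11.5% is 5.75% and half of 12.5% is 6.25%, with midpoint 6.0%. A difference of 6.0 with SD 8.0 needs 38.35, so 39 as stated. The normal approximation, n = 2(1.960 + 1.282)² × (SD/difference)², gives 38.
- Areal BMD: a difference of 3.5 with SD 4.0 needs 28.44, so 29 as stated (28 by the normal approximation).

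Both base figures are sound. The mismatch arises only at the dropout step.

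**Step 2: apply 30% dropout to each stated requirement**, rounding up.

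| Requirement | n / 0.70 | n × 1.30 |
|---|---|---|
| 24 | 34.3 → 35 | 31.2 → 32 |
| 29 | 41.4 → 42 | 37.7 → 38 |
| 32 | 45.7 → 46 | 41.6 → 42 |
| 39 | 55.7 → 56 | 50.7 → 51 |

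Only 39 × 1.30 gives 51. Division gives 56 per group, 112 in total: 5 more per group and 10 more overall.

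**Step 3: what 51 per group leaves.**

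- At 30% dropout: 51 × 0.70 = 35.7, about 36 per group.
- Largest dropout that still leaves 39: 1 − 39/51 = 23.5%.

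**Step 4: power if dropouts contribute no endpoint data** (t-test, two-sided 0.05).

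| Outcome | Difference, SD | 35 per group | 36 per group | 39 per group |
|---|---|---|---|---|
| Cortical area | 6.0, 8.0 | 87.1% | 88.1% | 90.5% |
| Areal BMD, low end | 3.5, 4.0 | 95.0% | 95.6% | 96.8% |
| Areal BMD, high end | 4.0, 4.0 | 98.5% | 98.7% | 99.2% |

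Over the halved losses at the two sites (5.75 to 6.25, SD 8.0), power for cortical area with 36 per group runs from 85.3% to 90.5%. The lean and fat mass requirement, at most 32, is also met by 36.

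**The case against.** The best defence is that little turns on this, and most of it stands. Cortical area is secondary. The loss is about two percentage points of power, and at the upper end of the halving assumption 36 per group still gives 90.5%. The article calls its 30% conservative, and up to 23.5% dropout leaves 39 intact. A man who leaves the programme is not necessarily lost to the analysis either: endpoint measures will be sought from withdrawals, outcomes are also measured at 26 weeks, and mixed models can use partial data. The 88% is therefore a worst case at the assumed dropout rate. None of this makes 51 the right answer to the stated sum, because the sample size section takes no credit for recovered data.

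It is also fair to object that the multiplication is not in the text. It is a strong inference, but the mismatch does not depend on it: 30% off 51 falls short of 39 however 51 was reached.

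A reader might go further and infer that the radius is badly underpowered, since its own figures (5.75%, SD 8.8) would need 50.2, so 51 men per group before any dropout. The documents do not support treating that as an error. The article openly chose a planning SD of 8.0, between the 8.8 and 7.4 it quotes, and nowhere promises 90% power at each site. On the tibia's own figures (6.25%, SD 7.4) only 31 would be needed. The radius result comes mostly from substituting a different SD: even with the full 39 men, its power would be about 81%.

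**Conclusion.** The point holds as a minor arithmetic inconsistency. The stated 51 per group does not retain the stated 39 at the stated 30% dropout; it retains about 36. The size is 5 men per group short of the 56 that division by 0.70 would give, about 9%.

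The effect is power of about 88% instead of 90% for cortical area. This assumes a t-test comparison, a 6.0% difference, SD 8.0, exactly 30% dropout and no endpoint data from those who leave.

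A reader might infer that the trial is too small for its main question. It is not: areal BMD needs 29 per group and has about 95–96% power with 35–36, even at the lower end of the assumed difference.

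**What to change.** Restate the dropout sentence in the Sample size calculation section in one of two ways:

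- 51 men per group retains 39 per group if dropout does not exceed 23%; or
- with 30% dropout about 36 per group remain, giving about 88% power for cortical area (6.0%, SD 8.0) and about 95% for areal BMD (3.5%, SD 4.0).

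Either version should note that endpoint measures obtained from withdrawals, as planned in the Statistical analysis section, may reduce the loss.

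The cost is one corrected sentence and a slightly less favourable power statement for a secondary outcome. Enrolment, design and analysis stay as they are.
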